### Recruitment {15}

Patient recruitment will take place in six centres in Belgium: Universitair Ziekenhuis Brussel, Universitair Ziekenhuis Gent, Universitair Ziekenhuis Leuven, AZ Turnhout, Vitaz and Jessa Ziekenhuis. Patients were recruited from April 4, 2022, onwards. Recruitment is expected to last for 2 years with an estimated rate of recruitment of 1 patient per centre per month. Nevertheless, recruitment will continue until the predetermined number of patients is included, regardless of the duration of the recruitment period. Depending on the rate of inclusion, we will contact other centres as well. Treating neurosurgeons or anaesthesiologists (regional coordinating investigator or his/her designee) will inform eligible patients about the project when patients are scheduled for a treatment trajectory with SCS.

## Assignment of interventions: allocation

### Sequence generation {16a}

Patients will be randomly allocated (1:1 ratio) to a personalised rehabilitation programme or usual care using a computer-generated random list. To reduce the predictability of a random sequence, a blocking procedure will be used including random block sizes of 2 and 4 patients. Randomisation will be stratified by investigational site and the duration of sick leave [67] (0 days–1 month, 1 month–1 year, 1–3 years and > 3 years).

### Concealment mechanism {16b}

The study coordinator is an unblinded researcher and is responsible for scheduling all appointments with therapists and patients and, therefore, will have access to the randomisation list (Excel file). The randomisation list is inaccessible for the outcome assessors and statistician. The study coordinator will not perform interventions nor measurements.

### Implementation {16c}

The study coordinator will generate the allocation sequence and is responsible for informing the patients into which group they are randomised. Additionally, the study coordinator will inform the patient about the next steps of the rehabilitation programme, in case the patient is randomised to this group.

## Assignment of interventions: blinding

### Who will be blinded {17a}

The statistician, outcome assessors and treating physicians (neurosurgeons or anaesthesiologists) will be blinded to group allocation. With regard to this, patients will be asked not to communicate with the assessors about the intervention received. Furthermore, at the end of each assessment, the success of assessor blinding will be examined by asking whether the assessor thought the patient had received the experimental or control intervention, including the percentage of certainty (i.e. 50% certainty means a pure guess).

### Procedure for unblinding if needed {17b}

The statistician and outcome assessors will not be unblinded during the trial. In case of a serious worsening of the clinical status of a patient, the treating physician will be unblinded.

## Data collection and management

### Plans for assessment and collection of outcomes {18a}

To optimise the study feasibility and to ensure data protection, the self-reported measures will be completed online using Qualtrics, in the hospital setting. The first assessment is at baseline, the second assessment takes place 6 weeks after IPG implantation, the third assessment immediately after the intervention of 14 weeks, the fourth assessment 3 months after the intervention, the fifth 6 months after the intervention and the sixth at 12 months after the intervention. See Table 1 for an overview of the specific questionnaires for each assessment and Fig. 2 for the participant timeline.

For the functional capacity evaluation, the assessors completed a 2-day training course with [name] (Rijksuniversiteit Groningen) to ensure a correct performance. As such, all assessors are certified to conduct these evaluations. The results of the functional capacity evaluation will be written down on paper during the assessments. Afterwards, the assessor will enter the data in a specific Excel file for this outcome measurement. A second assessor will control the data entry process.

### Plans to promote participant retention and complete follow-up {18b}

Patients receive a reminder of upcoming appointments and follow-up phone calls to promote participant retention and completion. For patients allocated to the rehabilitation programme, all sessions are scheduled to the patient’s wishes, needs and abilities, in agreement with the schedule of the therapists.

### Data management {19}

Data will be collected via web-based self-reported questionnaires that are provided to the patients on a tablet in the hospital. To avoid missing data, an error message will appear when a question is not filled in. Collected data will include answers to validated questionnaires related to the patients’ ability to work, work status and participation, health-related quality of life, pain intensity, physical activity/functioning, sleep quality, kinesiophobia, healthcare expenditure, anxiety, depression and self-management. In addition, patients will be asked about the duration of their symptoms and general demographic data. Written informed consent of the patients will be collected and provides the basis for the legal ground for the data management.

During the research, the persons responsible for data management and storage will be the predoctoral investigators. Following the research, the PI will be fully responsible for data management and storage. During the research, all obtained data will be stored on a dedicated page on Vrije Universiteit Brussel SharePoint (system-encrypted) with access limited to the investigators and supervisors. A back-up will be foreseen on a secure external hard drive. Following the research, all data will be relocated to the Vrije Universiteit Brussel Archive where it will be archived for 25 years. All possible personal identifiable data (vide infra) will be removed from the archived data.

Personal data will be processed in accordance with the ongoing European Union’s Data Protection Directive and regulation, the relevant Belgian legislation concerning data protection of July 30, 2018, and good clinical practice. As we collect personal identifiable data, the following steps are taken to limit unauthorised access. Informed consents will be preserved at a secure location at the Vrije Universiteit Brussel. Qualtrics (Qualtrics, Provo, UT) will be used for data collection to improve data protection as responses to questionnaires will only be accessible to the investigator. Collected data will be password protected. Personal identifiable and clinical trial data will be separated, with the latter receiving a unique participant ID. Access to informed consents, personal identifiable data and the link with the participant ID will be restricted to the investigators and supervisors and stored separately from the trial data. Eventual further dissemination of data will only occur in a pseudonymised or aggregated way.

The Vrije Universiteit Brussel supports the FOSB metadata standard (= dataset metadata schema defined by the Flemish Open Science Board) which can be mapped to the international DataCite metadata schema. At the project level, the general information (title, investigators, aim, objectives, concepts, hypotheses, funder), protocol, sampling procedure, instruments, hardware and software used to collect data, data handling log, accessibility of the data and data manipulations will be provided in research plans and publications. At the database level, an inventory of the files will be provided in a read-me file. At the data level, a codebook will be provided on how to handle quantitative variables together with the scripts to analyse the data.

### Confidentiality {27}

Participant identification codes will be used to link data to patients. The file containing the link between participant numbers and personal data (i.e. key) will be managed by the researchers and will be locked for access by others. As an additional security measure, the file linking the pseudonymisation to the original direct identifiers will be encrypted before it is uploaded to SharePoint.

### Plans for collection, laboratory evaluation and storage of biological specimens for genetic or molecular analysis in this trial/future use {33}

No biological specimens will be obtained during the conduct of the trial.

## Statistical methods

### Statistical methods for primary and secondary outcomes {20a}

Longitudinal mixed models will be used to evaluate and compare therapy effects. The primary outcome will be analysed as the difference in WAI score from baseline to the short-term primary endpoint immediately after the intervention and to the long-term primary endpoint at 12 months after the intervention (taking into account the longitudinal nature of the trial) between both groups. Baseline variables will be used as covariates. A similar strategy will be applied for secondary outcome measurements. The threshold for statistical significance will be set at *p*<0.05. Statistical as well as clinically significant differences will be defined, and the effect size will be determined.

### Interim analyses {21b}

No interim analyses will be conducted as we do not foresee any potentially serious outcomes.

### Methods for additional analyses (e.g. subgroup analyses) {20b}

Baseline data will provide cross-sectional results on work ability, work status, pain intensity, quality of life, physical activity, sleep quality, kinesiophobia, healthcare expenditure and functioning for the complete PSPS-T2 group and comparisons between possible subgroups. Based on the distribution of the data, group differences at baseline will be assessed using a parametric test or its non-parametric alternative at alpha lower than 0.05. Furthermore, correlation analyses will be performed to unravel correlations between the different outcome measures in patients with PSPS-T2, eligible for SCS. Correlation analysis will be performed with Pearson correlation coefficients if the assumption of a linear relation between two variables is met; otherwise, Spearman correlation coefficients will be calculated and tested at alpha < 0.05. Additionally, the association between self-reporting of the work ability (WAI; primary outcome measure) and objective measurements of work capacity (functional capacity evaluation; secondary outcome measure) will be determined.

Correlation analyses will also be performed to evaluate whether changes in physical and mental ability are related to secondary outcome measures, considering appropriate measures for multiple testing. Furthermore, based on the baseline data, we will try to determine predictive factors and which subgroup of patients will benefit the most from the interventional rehabilitation programme. For this, data obtained at the 12-month assessments will be dichotomised and the baseline variables used as explanatory variables. The predictive value of the secondary outcome measures at baseline for the treatment response at 12 months will be examined.

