#### Primary outcome

The ‘Work Ability Index’ (WAI) will be used as the primary outcome measure, which measures the work ability taking into account physical and mental parts of work as well as different diseases and their impact on work ability [44]. More specifically, the WAI consists of a questionnaire with 10 questions concerning current work ability compared with the lifetime best, work ability in relation to the job demands, number of current diseases diagnosed by a physician, estimated work impairment due to diseases, sick leave, self-prognosis of work ability and mental resources [45]. The total score of the WAI has a range from 7 to 49 with higher scores indicating higher work ability. This total score can further on be divided into four categories of work ability: poor (score from 7 to 27), moderate (score from 28 to 36), good (score from 3 to 43) and excellent (score from 44 to 49) [46].

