### Sample size {14}

Sample size calculation was performed using G*Power version 3.1.9.2 for evaluating differences in work ability between both interventions (the control and experimental intervention). Based on the least favourable design (two treatment arms, in which patients are measured three times) with a small effect size (*η*^2^=0.069; *d*=0.28) [66], a sample size of 112 patients is needed to reach a significant between-subject effect. This sample size calculation accounts for a 20% loss to follow-up after 1 year and for a SCS trial failure rate of 11.3%, according to Belgian reimbursement rules [5]. Calculations were based on two-tailed testing (alpha=0.05) with 85% power. Allocation ratio (N2/N1) was defined as 1, resulting in 110.3 patients (56 patients in the experimental group and 56 in the control group (*N*=112)).

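### The method given for finding who benefits most from the programme names no treatment-by-baseline interaction or usual-care contrast, so as written it identifies prognostic factors, not modifiers of benefit.

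*Protocol article*

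**What the plan says.** The protocol article, under Methods for additional analyses {20b}, states two linked aims: "we will try to determine predictive factors and which subgroup of patients will benefit the most from the interventional rehabilitation programme". The next sentence, tied to those aims by its opening words, gives the method: "data obtained at the 12-month assessments will be dichotomised and the baseline variables used as explanatory variables". A third sentence adds: "The predictive value of the secondary outcome measures at baseline for the treatment response at 12 months will be examined".

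The section does not mention treatment arm, an interaction term or a comparison with usual care for this analysis. It also does not say which 12-month variable is split, where the cut lies, what counts as response, or which arms enter the model.

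Elsewhere the article keeps the outcome as a score. Under Primary outcome, "The total score of the WAI has a range from 7 to 49". Under Statistical methods {20a}, "Longitudinal mixed models will be used to evaluate and compare therapy effects", with the WAI score compared between groups.

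**The concern.** The comparator throughout the trial is usual care. Benefit from the programme therefore means outcome under the programme minus outcome under usual care, and a baseline variable marks greater benefit only if that difference changes with it. This is an interaction question. Relating baseline variables to a 12-month status answers another question: who ends up well, for whatever reason.

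Two errors can follow. A variable that predicts outcome equally in both arms can be reported as a marker of benefit. A variable that truly modifies the effect can be missed. Dichotomising adds a loss of information in a trial that expects only about 80 evaluable patients.

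**Working it through.** **Plan's own figure.** The article gives no number for this analysis, so there is none to reproduce. The size of the data set follows from Sample size {14}: 112 patients, 20% loss to follow-up and 11.3% failure of the stimulation trial period give 112 × 0.80 × 0.887 = 79.5 evaluable, or about 40 per arm.

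**Step 1: what each model estimates.** Let A be the arm (0 usual care, 1 programme) and x a baseline variable, with mean outcome α + τA + βx + γAx.
- Programme effect for a patient with value x: τ + γx. Only γ concerns who benefits most.
- Slope on x in the programme arm alone: β + γ.
- Slope on x in both arms pooled 1:1 without interaction: β + γ/2.

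Neither slope isolates γ. If γ = 0, both equal β, so any prognostic variable tends to be flagged. If β = −γ/2, the pooled slope is zero and a real modifier is invisible. Splitting the outcome does not change this logic.

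**Step 2: purely prognostic variable (γ = 0).** All of the following are assumptions: 40 per arm, standard normal x, correlation r with the 12-month outcome, residual SD √(1 − r²), median split, logistic model, two-sided 0.05. The arm effect is 0.544 SD, from the article's η² = 0.069: f = √(0.069/0.931) = 0.272 and 2f = 0.544. Share of simulated trials in which x is flagged:

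| r | Programme arm only, split outcome | Both arms pooled, split outcome | Interaction test, continuous outcome |
|---|---|---|---|
| 0.1 | about 6% | about 10% | about 5% or less |
| 0.3 | about 30% | about 55% | about 5% |
| 0.5 | about 72% | about 95% | about 5% |

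Repeated runs differ by a few points (for example 51% to 55% for the pooled model at r = 0.3). The pattern does not change.

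**Step 3: pure modifier.** Slopes of −0.25 and +0.25 SD in the two arms (γ = 0.5, average slope 0), residual SD 1, 80 patients. From Step 1, the programme-arm slope is 0.25 and the pooled slope is 0. Share flagged:
- pooled, split outcome, no interaction: about 4% to 5%, which is no better than chance
- programme arm only, split outcome: about 20%
- interaction test on the split outcome: about 39%
- interaction test on the continuous outcome: about 57%

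**Step 4: cost of splitting a continuous score.** For a normal outcome cut so that a share p lies above the cut-point c, the relative efficiency is φ(c)²/[p(1 − p)]. The article gives no p, so a range is shown:
- p = 0.50: 0.3989²/0.25 = 0.637, loss 36%
- p = 0.30: 0.3477²/0.21 = 0.576, loss 42%
- p = 0.14: 0.2226²/0.1204 = 0.411, loss 59%
- p = 0.095: 0.1690²/0.0860 = 0.332, loss 67%

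The last two shares are the return-to-work percentages in the article's Background, used only to illustrate an uneven cut. At a median split, 79.5 evaluable patients carry the information of 79.5 × 0.637 ≈ 51.

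**The case against.** **Silence is not exclusion.** This is a condensed article, its analysis plan is not shown, and model terms for an exploratory analysis are often left to that plan. A reader might infer that the article rules out a control-arm contrast or an interaction. It does not: it names no model, no analysis set and no full list of terms. What stands is narrower. The article states an aim and attaches a method to it, and that method, as worded, does not answer the aim. Not knowing which arms enter does not help, because Step 1 shows that neither version without an interaction isolates the effect of interest.

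**Two aims, one of them properly served.** Relating baseline variables to 12-month status is a legitimate way to look for predictive factors in the prognostic sense. This objection stands, and the concern applies only to the aim of finding "which subgroup of patients will benefit the most from the interventional rehabilitation programme".

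**The figures depend on assumptions.** A reader might take the 72% as the error rate of the planned analysis. It is not. It belongs to r = 0.5 in a programme-arm-only model, and at r = 0.1 the figure is about 6%. Flagging a truly prognostic variable is also an error only if it is then called a marker of benefit. Likewise, a loss of about a third is the best case at a median split. The article does not say that the WAI is the variable split, and an outcome that is already yes/no would lose nothing.

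**Limited consequences.** The analysis is additional and tentatively worded. A reader might infer that referral would be misdirected, but the article does not tie these predictors to referral. Its Discussion bases adoption on the overall comparison.

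**Conclusion.** The mismatch between aim and method is real and worth correcting. For the question of who benefits most, the method as written identifies who does well at 12 months. With 40 per arm and no true interaction, it would flag a prognostic variable in about 6% to 72% of trials (programme arm only) or 10% to 95% (pooled) as r goes from 0.1 to 0.5, against about 5% for an interaction test. The pooled form has essentially no power for a pure modifier. These rates rest on a normal outcome, a median split and the stated correlations, none of which the article gives. If a continuous score is split, at least about 36% of the information is lost under normality.

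The point does not reach the primary between-group comparison or the sample size, and it does not show that the investigators intend to leave out the control arm.

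**What to change.** For the aim of finding who benefits most, state that both arms will be used and the 12-month outcome kept continuous. Arm-by-baseline interaction terms will be added to the longitudinal mixed model of Statistical methods {20a} for a short, pre-listed set of baseline variables. Report the interaction estimates with intervals and label them exploratory.

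For the aim of finding predictive factors, models without an interaction may stay, but their results should be called prognostic. If a dichotomised outcome is kept there, name the variable and the cut-point in advance.

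The change is one of wording and needs no new data. Its cost is low power: about 57% for a slope difference of 0.5 SD with 80 evaluable patients, and less for smaller differences. Fewer predictors will be declared, and a null interaction should not be read as proof that all patients benefit equally.

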#### Health economic analysis

First, a within-trial economic evaluation will be conducted. All costs of all patients will be considered, for the time horizon starting from IPG implantation until the end of the follow-up period. Intervention costs will be based on the study notes documenting the duration of each session per patient. The valuation of resource use is based on national tariffs. A societal perspective is adopted as indirect costs of productivity loss are a crucial part in the analyses. Health outcomes will be expressed in two ways. Effects are expressed in percentage physical and mental work ability, which is the primary outcome in this trial. Next, health outcomes will be considered expressed in utility using health state values from the general public. The comparator is usual care (control group). The overall result is expressed in an incremental cost-effectiveness ratio (ICER, i.e. incremental cost divided by the percentage increment in physical and mental work ability and incremental cost divided by the incremental QALY gained). Differences in cost between both groups will be analysed using generalised linear models. A modified Park test will be used to identify the appropriate link function. The point estimates of incremental costs and increment health benefits as described above (deterministic analyses) are subject to uncertainty which will be addressed in probabilistic analyses [68]. We will apply non-parametric bootstrapping to test for statistical differences in costs and health benefits to investigate the uncertainty around these outcomes and summarised in cost-effectiveness acceptability curves indicating the likelihood of the intervention to be cost-effective at any willingness-to-pay threshold. Reporting on the results of the health economic evaluation will be in line with the CHEERS II guidelines [69].

Besides the within-trial health economic evaluation, a model-based evaluation will be conducted in order to estimate the expected costs and health outcomes in both the control and intervention group beyond the follow-up period of the trial. A Markov model will be developed compliant to the commonly used guidelines [70]. We assume a cycle of 1 year in the model and apply a lifetime horizon. Lifetime incremental costs and QALYs will be the input for the ICER calculation. Discount rates of 3% for costs and 1.5% for utilities will be applied, which is in line with the Belgian guidelines [71]. The subsequent probabilistic analyses and reporting strategies are identical to those described above.

### Methods in analysis to handle protocol non-adherence and any statistical methods to handle missing data {20c}

Both intention-to-treat and per-protocol analyses will be conducted to check whether both definitions of the population will point towards similar results, which could demonstrate the robustness of the results. At first, the analysis will be performed on data as observed, since random effects mixed models enable us to conduct the analysis in case one valid measurement is included in the analysis. Hence, intermittent missing is not expected to substantially bias the results. To address possible informative drop-outs, a sensitivity analysis will be performed using multiple imputation, including all available information on background characteristics and outcome. All analysis will be performed in SAS or R.

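### The multiple imputation planned for informative drop-out is, as described, a missing-at-random method and cannot assess sensitivity to drop-out that depends on unseen WAI values

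*Protocol article*

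**What the plan says.** The protocol article's section on statistical methods {20a} sets the main analysis: "Longitudinal mixed models will be used to evaluate and compare therapy effects". On adjustment it says only "Baseline variables will be used as covariates".

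The section on missing data {20c} then takes three steps.

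- Main analysis: "At first, the analysis will be performed on data as observed, since random effects mixed models enable us to conduct the analysis".
- Gaps between visits: "Hence, intermittent missing is not expected to substantially bias the results".
- Drop-out: "To address possible informative drop-outs, a sensitivity analysis will be performed using multiple imputation, including all available information on background characteristics and outcome".

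The same section also compares intention-to-treat with per-protocol results. That changes who is analysed, not what is assumed about missing values. Nowhere does the article name a delta shift, reference-based imputation, a pattern-mixture or selection model, or a tipping point.

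On the amount of loss, the sample size section {14} says: "This sample size calculation accounts for a 20% loss to follow-up after 1 year". The outcomes section {12} makes the assessment 12 months after the intervention the long-term primary endpoint.

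**The concern.** Drop-out is informative when, after allowing for everything observed, it still depends on the value that was not seen. A likelihood-based mixed model on observed data is valid when that dependence is absent. Multiple imputation drawn from observed background and outcome data needs the same kind of assumption. The article therefore gives an analysis a purpose that the analysis, as described, cannot serve.

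The setting makes the question a practical one. Patients are told their allocation, and the WAI is a self-reported questionnaire. Only the programme arm is asked to attend 30 sessions and to refrain from starting other paramedical treatment. Reasons for leaving could therefore differ between arms. If they do, the 12-month contrast could be biased and the one analysis aimed at drop-out could carry the same bias.

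**Working it through.** **The plan's own figure.** The point disputes no printed number, but the 20% comes from the sample size, so that was reproduced first.

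- Inputs from section {14}: eta squared 0.069, two arms, three measurements, two-sided alpha 0.05, power 85%, 20% loss, 11.3% SCS trial failure. Assumed: correlation 0.5 between measurements.
- f = √(0.069 / 0.931) = 0.272.
- Between-groups F test with noncentrality f² × N × 3 / (1 + 2 × 0.5): N = 84 evaluable patients (power 0.855).
- 84 × (1 + 0.20 + 0.113) = 110.3, the printed value, raised to 112.

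**Effect used in the illustration.** The documents give no SD for the WAI, so the work is in SD units. For two equal groups d = 2f = 2 × 0.272 = 0.544. The article prints d = 0.28, which is close to f. The 0.544 is therefore a conversion, not a stated figure.

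**Illustration.** Assumed: baseline and two later WAI values, correlation 0.5, SD 1, true effect 0.544 at both later visits, 20% lost per arm before the last visit. Loss in usual care is random. Loss in the programme arm rises as the unseen 12-month WAI falls, with the log-odds slope per SD shown. Both methods use the same variables.

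| Slope, programme arm only | Mixed-model-type estimate | Multiple imputation |
|---|---|---|
| 0 | 0.549 | 0.550 |
| 1 | 0.668 | 0.666 |
| 2 | 0.737 | 0.739 |

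Both methods overstate the effect by 0.12 (0.67 − 0.54) to 0.19 SD (0.737 − 0.544 = 0.193), and they agree.

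A second simulation used a somewhat different drop-out model (about 23% lost in the programme arm, 20% in usual care) at a trial size of 100 patients. The means were 0.543 with full data, 0.721 from the likelihood and 0.720 from imputation. Across runs the last two correlated at 0.998, and their difference had an SD of 0.012.

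**Same mechanism in both arms.** With 20% lost in each arm by the same rule, the estimate is 0.54 to 0.55 at both slopes, so the contrast is not biased.

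**General size, without a drop-out model.** Let p be the fraction missing in an arm, and δ the amount by which the missing values differ on average from what missing-at-random predicts. The change in the contrast is p(programme) × δ(programme) − p(control) × δ(control). With 20% missing and a departure in the programme arm only:

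| δ (SD) | Change in effect (SD) |
|---|---|
| −0.25 | 0.20 × −0.25 = −0.05 |
| −0.5 | 0.20 × −0.5 = −0.10 |
| −1.0 | 0.20 × −1.0 = −0.20 |
| −1.5 | 0.20 × −1.5 = −0.30 |

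These changes do not depend on the true effect. A change of 0.10 SD is 0.10 / 0.544 = 18% of the converted effect, or 0.10 / 0.28 = 36% if the printed 0.28 is read as a standardised difference. With 20% missing in both arms and equal δ, the terms cancel.

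**The case against.** **Missing-at-random is inferred.** The article never uses the term. Multiple imputation is also the usual vehicle for delta-adjusted and reference-based analyses, and a separate statistical analysis plan, not among the documents, might add one. This limits certainty about what will be done. It does not repair the published sentence, which names both method and purpose and includes no departure from missing-at-random.

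**The two analyses need not coincide.** The mixed model is described with baseline covariates only, whereas the imputation may draw on more, possibly including post-baseline secondary outcomes. In a variant where programme-arm loss was driven by such a variable (assumed correlation 0.6 with 12-month WAI), the estimate without it was 0.60 to 0.63, and imputation with it gave 0.55. This stands: the planned imputation can be useful. When loss depended on the unseen WAI itself, however, the extra variable helped little (0.67 to 0.64 at slope 1, 0.74 to 0.71 at slope 2).

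**No analysis can detect informative drop-out.** A reader might infer that another method would have detected it. None can from observed data alone. The fair standard is whether an analysis shows how the conclusion changes as the assumption is relaxed.

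**The bias is a chosen scenario.** A reader might infer that the trial's result will be too favourable by 0.12 to 0.19 SD. The documents do not support that: the slopes and the one-arm mechanism are assumptions, and the bias disappears when both arms behave alike.

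**Robustness is not claimed for this comparison.** A reader might infer that the article promises to present agreement between mixed model and imputation as robustness. It uses that idea only for intention-to-treat against per-protocol.

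**The 20% is loss to follow-up after 1 year.** It is not a rate of stopping the programme and may include patients who completed it. No loss figure is given for the short-term primary endpoint.

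**Conclusion.** The point holds as a mismatch between a stated method and its stated purpose. It concerns the sensitivity analysis and does not show that the primary mixed model is wrong. As described, the imputation can test whether a richer missing-at-random model changes the answer. It cannot assess sensitivity to drop-out that depends on unseen WAI.

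The firmest measure of what is left unexamined is 0.10 SD for each 0.5 SD departure in one arm, given the protocol's 20% loss falling in that arm. The 0.67 to 0.74 SD figures show only that both methods can share the same bias. They rest on the assumed correlation, slopes, one-arm mechanism and converted effect of 0.54 SD. The change should be made before the data are analysed.

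**What to change.** In section {20c}, describe the planned multiple imputation as a check under missing-at-random, and list the auxiliary variables it adds to those in the mixed model.

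Then add a sentence such as: sensitivity to informative drop-out will be assessed by delta-adjusted multiple imputation of WAI, with imputed values shifted over a prespecified range separately in each arm, and the shifts at which the conclusion changes will be reported. Apply this at least at the 12-month primary endpoint, where the 20% loss is expected; the short-term primary endpoint can be included if loss there proves material.

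Control-based imputation is an optional addition. It assumes that programme patients resemble usual care after they are lost, which is open to question for those who completed the programme.

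The cost is a change of wording and a few hours of programming in SAS or R, with no new data or visits. The supporting estimate may turn out less favourable to the programme.
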